### Analysis

The primary outcomes will be analyzed with negative binomial regression for panel data, using the Stata *xtnbreg *procedure [41]. For the proportions of students exceeding recommended upper limits we will use generalized linear mixed models with the *xtmelogit *procedure [42,43]. The results will be presented as readily interpretable risk ratios and odds ratios respectively. Participants will be analysed in the group to which they were randomized (intention to treat), with multiple imputation methods used for any missing follow-up data [44,45].

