## Methods/Design

### Design

The study consists of two parallel, multi-site, double blind, individually randomised controlled trials. The trials are recruiting Māori and non-Māori students aged 17-24 years from seven of New Zealand's eight universities. Figure 1 shows the trial design.

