### Instrument, randomisation, and intervention

Respondents will visit the study website and be presented with an introductory page followed by one page of five questions concerning (1) gender, (2) age, and the three items of the AUDIT-Consumption subscale [12]: (3) frequency of drinking; (4) number of standard drinks (defined as containing 10 g ethanol) consumed per typical drinking occasion; and (5) frequency of having six or more drinks per occasion. The AUDIT consumption subscale (AUDIT-C) is a valid screening tool, with specificity and sensitivity similar to the full AUDIT [29] and its psychometric performance has been previously evaluated in online studies with university students [30].

Upon clicking the submit button on this page, AUDIT-C scores will be calculated. Those who score ≥ 4 on the AUDIT-C will be randomly allocated by the web server to either the intervention or control group. The control group will be sent to a *Thanks *page at this point and advised that they will be contacted again by e-mail in second semester to complete a similar brief questionnaire.

The rationale for limiting the control group's alcohol questions to three items is that previous research shows that simply asking questions about alcohol consumption can act as intervention, producing reductions in self-reported drinking levels [31]. Indeed, such effects have been shown for the AUDIT alone [32].

Those in the intervention group will continue and be asked AUDIT items 4-10, and additional questions concerning the largest number of standard drinks consumed on one occasion in the last four weeks, the duration of the drinking episode in hours, and their body weight (for the purpose of estimating peak blood alcohol concentration). They will also complete the Leeds Dependence Questionnaire (LDQ; 10 items) [33]. The psychometric performance online of both the AUDIT and the LDQ has been confirmed in previous study with university students [34].

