### Follow-up

A high follow-up rate is clearly vital to the success of e-SBI trials and several approaches have been adopted to maximise this. In the second semester, approximately five months later, all participants will be invited to complete a brief on-line follow-up assessment, with the chance to win a $500 supermarket voucher or an Apple iPad. The assessment will include questions concerning the frequency of drinking and amount consumed per typical drinking occasion, all with a reference period of the last 4 weeks. In addition, participants will be presented with the five questions comprising the Academic Role Expectations and Alcohol Scale (AREAS) [35], plus questions concerning their subjective experience of the study.

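### The named panel negative binomial command does not match the dispersion model used to size the trial, and its output is labelled as risk ratios although it gives ratios of means

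*Protocol article*

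**What the plan says.** On the count and score outcomes, the Analysis section of the protocol article states: "The primary outcomes will be analyzed with negative binomial regression for panel data, using the Stata" xtnbreg procedure. On the two drinking-limit outcomes it states: "For the proportions of students exceeding recommended upper limits we will use generalized linear mixed models with the" xtmelogit procedure. On reporting: "The results will be presented as readily interpretable risk ratios and odds ratios respectively". The word *respectively* ties risk ratios to the negative binomial results and odds ratios to the logistic ones. The section does not say what forms the panel.

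The data structure is described elsewhere. Design: "The study consists of two parallel, multi-site, double blind, individually randomised controlled trials", recruiting at "seven of New Zealand's eight universities". Follow-up: "In the second semester, approximately five months later, all participants will be invited to complete a brief on-line follow-up assessment". The follow-up drinking questions are "all with a reference period of the last 4 weeks". Before randomisation, both arms give gender, age and the three AUDIT-C items. Controls answer no further alcohol questions at baseline, and the article explains this under "The rationale for limiting the control group's alcohol questions to three items".

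The sample size section uses mean weekly volumes of 16.1 (SD 15.9) and 13.6 (SD 14.0), 5% significance, 80% power and a dispersion factor of 0.92, and arrives at 547 per group at follow-up.

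**The concern.** The same article names both a sizing model and an analysis command. If they imply different variance structures, the 80% power claim does not carry over to the planned analysis. The estimate itself can also shift. In the standard panel negative binomial likelihood the treatment coefficient governs the shape of the distribution as well as its mean, so a wrong variance form can pull the estimated ratio away from the true ratio of means. Volume is the outcome on which the trial was sized, and the Discussion says the findings could inform a decision on implementation.

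The label is a separate matter. A reader told that a risk ratio is 0.845 will think of the chance of an event, whereas the number compares average drinks per week.

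**Working it through.** **1. Reproduce the plan's figure.** Inputs are from the sample size section: means 16.1 and 13.6, dispersion k = 0.92, 5% significance (taken as two-sided, since sidedness is not stated), 80% power. With one value per person and quadratic dispersion,

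n per group = (1.960 + 0.842)² × (1/16.1 + 1/13.6 + 2 × 0.92) / [ln(13.6/16.1)]²
= 7.849 × 1.9756 / 0.02848 = 544.5, so 545.

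This is within two of the stated 547. The sizing therefore assumes one observation per participant and no panel structure.

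**2. Confirm the dispersion form.** Under the quadratic form, variance = mean + k × mean².

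- Control: 16.1 + 0.92 × 16.1² = 254.6, SD 15.96 (stated 15.9).
- Intervention: 13.6 + 0.92 × 13.6² = 183.8, SD 13.56 (stated 14.0).

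So 0.92 is a quadratic dispersion parameter. The implied variance-to-mean ratios are 254.6/16.1 = 15.8 and 183.8/13.6 = 13.5. A proportional-variance model requires one common ratio in both arms.

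**3. If the panel is the university.** In the standard panel negative binomial likelihood, variance = mean × (1 + δ) within a panel, with a common δ for both arms. As a simplification I ignored site differences and the random layer across sites, and fitted this form by maximum likelihood to data generated from the quadratic model in step 2.

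| Quantity | Quadratic form | Proportional form |
|---|---|---|
| Mean ratio estimated | 13.6/16.1 = 0.845 | about 0.890 |
| Reduction shown | 15.5% | about 11.0% |
| Power at 547 per group (simulated, likelihood-ratio test) | about 77% | about 61% |

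The loss is (15.5 − 11.0)/15.5, or about 30% of the planned reduction. Repeated simulation runs gave 60% to 62% for the proportional form and 76% to 78% for the quadratic form, which is within Monte Carlo error. With no treatment effect both arms share one mean and the two forms coincide. The distortion is therefore towards no effect and does not create false positives.

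**4. If the panel is the participant.** There is one follow-up. AUDIT-C asks about frequency and typical quantity at baseline, but the four-week reference period is given only for the follow-up questions, and AREAS is described only at follow-up. A like-for-like baseline value that would make a two-point panel is not described.

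**5. The label.** The Outcomes section lists weekly volume, frequency, quantity per occasion and AREAS score, and none of these is a probability. An exponentiated negative binomial coefficient for them is a ratio of means (or rate ratio), with a planned value of 0.845 for volume.

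**The case against.** The strongest reply is that the article never says the participant is the panel. The named commands handle any grouping, and with seven universities and individual randomisation the university is a natural unit. One follow-up value per person is then no obstacle. This stands. A reader might infer that the plan applies repeated-measures models to single observations, or that its random intercept cannot be estimated. The text does not support that, and leaving the grouping unit to a separate analysis plan is ordinary. Choosing university as the unit does not, however, remove the variance mismatch in step 3, because the command itself is fixed in the article.

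A second reply is that the variance form is a property of the software that the documents do not describe. That is fair as a caveat. The calculation assumes the usual likelihood version of the panel model. A population-averaged fit would not share that form, and the article does not say which is meant.

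A third reply is that odds ratios from a logistic model are standard and correctly named. This also stands. A reader might infer that reporting only odds ratios for the guideline outcomes is an error; it is not. How far they would differ from risk ratios cannot be read from the article, which gives no proportions above the limits. Model-implied values from the same inputs are 41.2% against 34.9% above 14 drinks per week (risk ratio 0.85, odds ratio 0.77). Those figures apply the women's limit to everyone. At the men's limit of 21 they are 26.6% against 20.8% (risk ratio 0.78, odds ratio 0.73).

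Finally, the word *risk* changes no estimate or test. That is true; the label affects interpretation only.

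**Conclusion.** The concern holds in two parts. The named count command, in its standard likelihood form, conflicts with the quadratic dispersion on which the trial was sized. On the plan's own inputs the estimated mean ratio moves from 0.845 to about 0.89, and power at 547 per group falls from about 77% to about 61%. These figures are for weekly volume only and rest on three assumptions: a two-sided test, no site effects, and the likelihood version of the model. They indicate the direction and rough size of the mismatch and do not predict the trial's result. The 547 itself reproduces and is not in question.

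The label *risk ratios* is wrong for the negative binomial outcomes as the article states it, whatever the panel unit turns out to be.

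**What to change.** - Analyse the single follow-up value of each count or score outcome with mean-dispersion negative binomial regression (nbreg, robust standard errors), with university in the model. This matches the sizing model.
- Report the result as a ratio of means or rate ratio.
- If a grouped model is kept for any outcome, name the grouping unit and the variance form.
- Optionally, add standardised risk differences or risk ratios beside the odds ratios for the two guideline outcomes.

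The cost is a few reworded sentences in the Analysis section and simpler code. No new data and no change to the sample size are needed.

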### Ethical approval

Ethical approval has been given by the Multi-region Ethics Committee, Ministry of Health (Ref: MEC/10/01/009).

## Discussion

A key attribute of a successful public health intervention is the extent it can be scaled up so that there are measurable impacts at a population level. This requires a series of stages in the supporting research. This trial has the potential to address a number of issues. First, if effects of the THRIVE trial [38], on which this trial is based, are replicated, there will be evidence that pro-actively delivered e-SBI is effective across a range of student cultures spanning two countries. This would be an important development given the largely efficacy evidence base on e-SBI to date. The findings would have clear applicability to university health promotion programs for this serious and pervasive health compromising behaviour.

Second, effect estimates will be produced separately for Māori and non-Māori. This would be the first study of a population intervention anywhere adopting the Equal Explanatory Power model on this scale for improving indigenous people's health. Critically, the findings could inform a decision as to whether to implement this intervention for Māori and non-Māori students in New Zealand.

Methodological strengths include the use of proven recruitment procedures, a validated screening instrument, up-to-date normative data, and a trial design that minimises the potential for assessment effects to bias estimates of intervention efficacy.

The major methodological challenges relate to recruitment and retention of participants. We plan to invite more than 15,000 individuals to participate and we are aware of no brief intervention trial ever having been conducted on this scale. Encouragingly, previous experience in the THRIVE trial in Australia [20] and surveys of New Zealand university students [22] show that using appropriate methods it is possible to recruit thousands of students within a few weeks and that the approach can be scaled up to include several university campuses.

The primary threat to validity will arise from any failure to retain a large proportion of participants for follow-up assessment. In the New Zealand primary care-based trials of e-SBI [16,17], in which recruitment was conducted face-to-face, retention was excellent: 85% at 12 months. In the THRIVE trial [38], however, where recruitment was online, only 65% of participants were retained at six months. Fortunately, there was no evidence of attrition bias, however, the potential for attrition to bias effect estimates increases as retention falls. Accordingly, we will adopt a method of obtaining a minimum response from those lost to follow-up with a view to estimating the degree of any attrition bias and potentially adjusting for it.
